### Double-blinding

Participants and investigators will be blinded. Packaging and labelling of drugs will be conducted by medical staff independent from the research team. Neither the subjects nor the investigators will know the types of drugs taken by each subject. Blind codes will be broken after all processes are completed, or at the request of the Human Research Ethics Committee, or if there is a serious adverse event.

### Quality control

To ensure the quality of the research, this study protocol has undergone multiple modifications and revisions by relevant digestive disease specialists, experienced surgeons, professional statisticians, and research methodologists. To maintain data objectivity, we will ensure that the observers and statisticians are blinded. The whole process will be monitored by independent quality inspectors. The CRF will be completely strictly and in accordance with the CRF instructions; in addition, the original medical history and data recorded in the CRF are not permitted to be altered; any modifications must be explained in detail and accompanied by the signature of the individual who made the change. All laboratory data must be recorded thoroughly, significantly abnormal data checked repeatedly and the physician will be required to make any necessary instructions in response to such information. Since any remaining medicine will be recovered and recorded, we will be able to objectively determine patient compliance.

### Outcome measures

1. Primary outcome measures: time to first flatus, time to first defecation, time to first bowel sounds, time to consuming liquid/semi-liquid/general diet

2. Secondary outcome measures: gastrointestinal symptoms, such as abdominal distention and pain, nausea, vomiting; serum hormone levels, including ghrelin, motilin, corticotropin-releasing hormone, and bradykinin; electrogastrogram

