**Methods/design:**

This double-blind, randomized controlled clinical trial aims to recruit patients who have undergone abdominal surgery and experienced postoperative dysmotility to evaluate the efficacy and safety of XBP for preventing POI and accelerating recovery. The research will tackle the common problem of slow recovery of gastrointestinal function after surgery. The participants will be patients who undergo laparoscopic radical resection of rectal carcinoma or laparoscopic panhysterectomy of a benign lesion. Primary outcome measures will be time to first flatus, defecation, normal bowel sounds, and liquid/semi-liquid/general diet. Good Clinical Practice (GCP) standards of efficacy and safety will also be evaluated, along with objective investigation of the mechanism of action of ghrelin.

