### Sample size estimation

The study consists of two groups: the sample size estimation was based on our previous prospective clinical study performed in patients who underwent gynecologic transabdominal surgery [1]. Time to first flatus was assumed to be 22.06 and 26.78 h between the XiangBin granules and the placebo groups, respectively. The minimum detectable difference, 4.72 h, was used to estimate the value of the overall parameters. PEMS 3.1 Software for Windows was used to randomly assign the patients to the treatment or the placebo group. The rounded sample size for each group was 89. Assuming a 15% dropout rate, the final sample size would be 105 for each group. Therefore, 420 participants who have undergone laparoscopic radical resection of rectal carcinoma and laparoscopic panhysterectomy of benign lesions will been recruited.

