### Data collection and statistical analysis

Data will be collected from participants via daily face-to-face and telephone interviews and recorded in the CRFThe statistical package, Epidata 3.1, will be used for data entry. Two people will perform data entry independently, and they will be trained in advance and pass a test before they begin the work. The data will then be transferred to Statistical Package for the Social Sciences (SPSS) software for data analysisThe statistical analyses were pre-specified and performed on an intention-to-treat (ITT) basis. The ITT analysis will include all patients who were randomly recruited, and the per-protocol (PP) analysis includes patients who completed the study and did not have major protocol violations. All analyses are based on the ITT population, and the result of the ITT analysis is compared with the PP analysis to assess the sensitivity. All missing data are analyzed using the last observation carried forward (LOCF) imputation method. Changes from baseline in outcome measurement among the two groups are analyzed using analysis of variance (ANOVA) or the Kruskal-Wallis test when appropriate. The Bonferroni methods for multi-comparisons are performed if the tests are statistically significant. Safety analysis is analyzed mainly using descriptive statistics. All statistical tests are in a two-tailed t test at a 5% level of significance (Additional file 1).Data will be analyzed by an independent statistician. Data for continuous variables are reported using mean (standard deviation; SD) for normally distributed data or median (range) for skewed data. Data for categorical variables are expressed as number (percentage). Intergroup differences are assessed for significance using Student’s *t* test for normally distributed continuous variables or the Mann-Whitney U test for skewed continuous variables. Intergroup differences in categorical data are assessed using the *χ*^2^ test or Fisher’s exact tests (two-tailed), as appropriate. Length of hospital stay is calculated using Kaplan-Meier analysis to compare differences between groups. Data are analyzed using SPSS 19.0 (IBM, Armonk, NY, USA), with the threshold of significance defined as a two-tailed *p* < 0.05.

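### Four to six unranked primary recovery times are each tested at two-sided 5%, and the only multiplicity rule names no family of endpoints

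*Protocol article*

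**What the plan says.** The Outcome measures section gives the primary set as "Primary outcome measures: time to first flatus, time to first defecation, time to first bowel sounds, time to consuming liquid/semi-liquid/general diet". The Abstract repeats it with one change: "Primary outcome measures will be time to first flatus, defecation, normal bowel sounds, and liquid/semi-liquid/general diet". Neither place ranks the outcomes, combines them, or says whether one or all must succeed. The opening paragraph of Methods/design also speaks of normal, not first, bowel sounds.

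The Data collection and statistical analysis section sets the level test by test: "All statistical tests are in a two-tailed t test at a 5% level of significance". It ends by restating a two-tailed threshold of 0.05. Its only multiplicity wording comes directly after ANOVA and Kruskal-Wallis are named for changes from baseline: "The Bonferroni methods for multi-comparisons are performed if the tests are statistically significant".

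The Sample size estimation section says "The study consists of two groups" and bases the calculation on one endpoint: "Time to first flatus was assumed to be 22.06 and 26.78 h between the XiangBin granules and the placebo groups, respectively". It does not call that endpoint the single primary.

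**The concern.** The trial calls itself pivotal, so its primary result is meant to carry a confirmatory claim. With several equal primaries, each at the full 5%, and no stated rule for combining them, the article does not fix what a positive trial is. Nor does it show that the overall error rate is held at 5%. Whoever reports the result could point to whichever time crossed the threshold.

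The Bonferroni sentence looks like protection but names neither a family nor a divisor. The two bowel-sound descriptions add a second freedom, because the first sound heard and the return of normal sounds can be different events at different times.

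**Working it through.** **Inputs from the article.** Number of primaries k = 4 (diet as one item) or 6 (liquid, semi-liquid and general diet counted separately), from Outcome measures. Level per test 0.05 two-sided, from Data collection and statistical analysis. Two arms, 22.06 h against 26.78 h, 89 per group, 15% dropout, 105 per group and 420 in total, from Sample size estimation.

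**Assumptions, not in the article.** No true effect on any primary; any one significant primary counts as success; a common correlation ρ between the test statistics, shown at 0, 0.5 and 0.7.

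**1. The plan's own figures.** 26.78 − 22.06 = 4.72 h, as stated. 89 / (1 − 0.15) = 104.7, rounded up to 105, as stated. The 89 itself cannot be checked, because no SD or power is given. All of this concerns flatus; no other primary enters the calculation.

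**2. What the Bonferroni sentence does.** Two groups form 2 × 1 / 2 = 1 pair. Read as a post hoc pairwise step, the divisor is 1 and the adjusted level is 0.05 / 1 = 0.05, so nothing changes.

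**3. Chance of at least one false-positive primary, independent tests.**
- Either direction: 1 − 0.95^4 = 0.185; 1 − 0.95^6 = 0.265.
- In favour of XBP only (2.5% per test): 1 − 0.975^4 = 0.096; 1 − 0.975^6 = 0.141.

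**4. Correlated tests.** For equicorrelated normal statistics with c = 1.96, the chance is 1 − ∫ φ(u) [Φ((c − √ρ·u)/√(1−ρ)) − Φ((−c − √ρ·u)/√(1−ρ))]^k du. For results favouring XBP only, the second Φ term is dropped. By numerical integration:

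| ρ | Either direction, k = 4 | Either direction, k = 6 | Favouring XBP, k = 4 | Favouring XBP, k = 6 |
|---|---|---|---|---|
| 0 | 18.5% | 26.5% | 9.6% | 14.1% |
| 0.5 | 15.6% | 20.7% | 7.8% | 10.4% |
| 0.7 | 13.0% | 16.4% | 6.5% | 8.2% |
| Nominal | 5% | 5% | 2.5% | 2.5% |

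At ρ = 0.8 the either-direction figures are still 11.4% and 13.9%.

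**5. Only if the surgery types were tested separately.** The total of 420 = 4 × 105 would fit a separate sizing for each surgery type, but the article does not say that each is tested. If six primaries were tested in each type, with ρ = 0.5 within a type and the types independent, the chance in either direction would be 1 − (1 − 0.207)² = 0.37.

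**6. The bowel-sound outcome.** Outcome measures times the first bowel sounds; the Abstract and the opening of Methods/design time normal bowel sounds. No definition connects the two.

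**The case against.** The strongest reply is that the article is a condensed account. An analysis plan and a supplementary file are not shown, and alpha allocation is often settled there. That would excuse silence. Here, however, the article does state a primary set, a level for every test and a multiplicity rule, and these do not fit together. A hierarchy elsewhere would have to override them.

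A second reply is that the Bonferroni sentence may be meant for the endpoints. If so, making it conditional on significance does no harm: p < 0.05/k already implies p < 0.05, so the rejections are those of ordinary Bonferroni. This stands as far as it goes. A reader might infer that the plan certainly has no correction, and the text does not support that. It supports a rule whose family is undefined and whose natural reading is empty with two arms.

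Three other strong readings also fail:
- A reader might infer a 16% to 26% chance of falsely claiming that XBP works. Those rates count significance in either direction, so they include results favouring placebo. They also depend on the number of tests and on a correlation that the article does not give. Diet steps in particular may be strongly correlated.
- A reader might infer that the plan lets any single win count as success. It gives no success rule. If all primaries had to succeed, there would be no inflation.
- A reader might infer that Bonferroni over six endpoints would cost too much power. That needs an unstated design power, an SD solved back from it, and separate analysis by surgery type. If 80% power is assumed and all 420 are pooled (420 × 0.85 / 2, about 178 evaluable per arm), power for flatus after that correction is about 91%. Power is therefore not the argument for a single primary. The argument is that flatus is the only endpoint used for sizing.

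**Conclusion.** The concern holds in this form: four to six unranked primaries, each at two-sided 5%, with a multiplicity sentence that does not define a family and, on its natural reading, adjusts nothing.

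If any one significant primary counts as success, the chance of at least one false-positive primary lies between 13.0% and 26.5% in either direction over correlations of 0 to 0.7. In favour of XBP it lies between 6.5% and 14.1%, against a nominal 2.5%. The any-one-wins rule and the correlations are assumptions, so the exact size is uncertain; under that rule the rate exceeds nominal in every case in the table. The 37% figure holds only on the further assumption of separate testing by surgery type.

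The conflict between first and normal bowel sounds is a contradiction in the text and depends on no calculation.

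**What to change.** - Name time to first flatus as the single primary outcome, tested at two-sided 5%.
- Make the remaining times key secondary outcomes, tested in a stated fixed sequence or by Holm, and only if flatus is significant.
- Replace the conditional Bonferroni sentence with that rule.
- Reconcile the bowel-sound wording in the Abstract, the opening of Methods/design and Outcome measures, so that one defined event is used throughout.
- Make the change before unblinding, and record it, with its date, in the registry. The article reports recruitment as ongoing.

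The cost is a protocol and registry amendment. The trial also gives up the option of calling a win on another recovery time alone a primary success. No new data collection is needed.

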### Safety assessment

The three routine tests (blood, urine, stool), liver and kidney function tests, and an electrocardiogram will be performed both before and after treatment. Adverse events occurring at any time during the treatment or follow-up phases will be observed and recorded in detail.

### Sample size estimation

The study consists of two groups: the sample size estimation was based on our previous prospective clinical study performed in patients who underwent gynecologic transabdominal surgery [1]. Time to first flatus was assumed to be 22.06 and 26.78 h between the XiangBin granules and the placebo groups, respectively. The minimum detectable difference, 4.72 h, was used to estimate the value of the overall parameters. PEMS 3.1 Software for Windows was used to randomly assign the patients to the treatment or the placebo group. The rounded sample size for each group was 89. Assuming a 15% dropout rate, the final sample size would be 105 for each group. Therefore, 420 participants who have undergone laparoscopic radical resection of rectal carcinoma and laparoscopic panhysterectomy of benign lesions will been recruited.

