## Background

It has been shown that the small intestine recovers more quickly after surgery (0–24 h) than the stomach (24–48 h) and colon (48–72 h) [1]. Postoperative ileus (POI) can occur as a common complication of anesthesia and surgery after various types of abdominal surgery [2]. The neuronal reflex required for gastrointestinal motility can be temporarily inhibited during surgery, causing nausea, vomiting, abdominal distension, and delaying the postoperative time to first flatus and defecation [3]. Numerous clinical research studies have shown that failure to restore adequate bowel function can result in a series of complications, including infection and intestinal adhesion, leading to prolonged hospital stay, and increased costs and readmission rates. The incidence of POI after abdominal surgery is 10–30% [4]. Reliable data demonstrate that the total cost of surgery can double for patients with, compared with those without, POI ($16,612 vs. $8316; *p* < 0.05) [5]. The Chinese herbal medicine *Xiangbin* prescription (XBP) has been proven to accelerate the recovery of bowel function [6]; however, its use lacks compliance with Good Clinical Practice standards. To extend and ensure the appropriate use of traditional Chinese medicine (TCM), rigorous studies are needed to ensure the safe and effective use of Chinese herbal medicines for the improvement of gastrointestinal motility.

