## Methods/design

This pivotal study has been designed as a double-blind, randomized controlled, clinical trial. Patients who have undergone laparoscopic radical resection of rectal carcinoma or laparoscopic panhysterectomy for benign lesions, between March 2015 and June 2018 at Guangdong Provincial Hospital of Traditional Chinese Medicine, will be selected and invited to participate. Patients will be randomly assigned to either the XBP group or the placebo group using numbers randomly generated by the webtool http://www.gztcmgcp.com/sjxt/login.asp. The efficacy and safety of XBP for patients who have undergone abdominal surgery will be evaluated by comparing various indices in the two different groups, including: time to first passage of flatus, first defecation, normal bowel sounds, and consumption of a liquid/semi-liquid/general diet. The study aim is to determine whether XBP can improve the speed of restoration of postoperative gastrointestinal motility. The study protocol has been approved by the Ethical Committee of the Second Affiliated Hospital of Guangzhou University of Traditional Chinese Medicine (Guangdong Provincial Hospital of Traditional Chinese Medicine). Written informed consent was obtained from all volunteers, and the study conformed to the ethical principles set forth by the Declaration of Helsinki. The study protocol is registered at the Chinese Clinical Trial Registry (http://www.chictr.org.cn/showproj.aspx?proj=5412).

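### Two groups of 105 make 210, yet the protocol recruits 420; the factor of two is not stated and the analysis described does not use it

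*Protocol article*

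**What the plan says.** All of the sizing is in the protocol article under Sample size estimation. It opens with "The study consists of two groups: the sample size estimation was based on our previous prospective clinical study", a study in gynaecological transabdominal surgery. The planning values are "Time to first flatus was assumed to be 22.06 and 26.78 h between the XiangBin granules and the placebo groups, respectively", and "The minimum detectable difference, 4.72 h, was used to estimate the value of the overall parameters". The result is "The rounded sample size for each group was 89". The closing step is "Assuming a 15% dropout rate, the final sample size would be 105 for each group. Therefore, 420 participants who have undergone" either rectal resection or hysterectomy.

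Elsewhere the design has two arms. Methods/design says "Patients will be randomly assigned to either the XBP group or the placebo group". Trial procedure and Randomization both mention stratification, but neither names the strata.

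Data collection and statistical analysis places all randomised patients in one intention-to-treat population. It compares the two groups by t test or Mann-Whitney test at a two-sided 5% level. It describes no comparison within a surgery type, no interaction test and no division of alpha between the two operations. Its Bonferroni sentence concerns multiple comparisons that follow a significant test and does not mention surgery type.

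**The concern.** The total is presented as the consequence of a two-group calculation, but it is exactly double what that calculation gives. The reader must supply the missing factor, and the natural candidate, the two operations, implies a different trial from the one in the analysis section. Sizing each operation separately makes sense if each is to be tested separately, whereas the analysis described pools them.

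What is at stake is what the trial's stated size means. With one pooled comparison, the justification given covers only half of the patients, and the planned power and detectable difference are not those of the trial being run. With one comparison per operation, the analysis section lacks the tests for which the trial was sized, along with any rule for the error rate across them.

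**Working it through.** **Inputs.** From Sample size estimation: two groups; means 22.06 h and 26.78 h; difference 4.72 h; 89 per group; 15% dropout; 105 per group; total 420. From the statistical analysis section: alpha 0.05, two-sided. The article states neither the SD nor the power, so both are treated as unknown below.

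**Reproducing the plan's own figures.**

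- Difference: 26.78 − 22.06 = 4.72 h. Agrees.
- Dropout: 89 / (1 − 0.15) = 104.7, rounded up to 105. Agrees. The alternative convention, 89 x 1.15 = 102.35, gives 103, so the plan used division.
- Total: 2 x 105 = 210. The plan says 420. Does not agree.
- Only 4 x 105 = 420 gives the stated figure, that is 2 arms x 2 surgery types x 105. No choice of dropout convention closes a twofold gap.

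**Reading 1: all 420 in one two-arm comparison.** There are 210 per arm, and 210 x 0.85 = 178.5, so about 178 evaluable per arm. This is 2 x 89.

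- For a fixed SD, alpha and power, the detectable difference scales with 1/√n. It becomes 4.72 / √2 = 3.34 h. This needs neither the SD nor the power.
- Power for 4.72 h does need an assumption. From n = 2·SD²·(1.96 + z)² / 4.72² with n = 89, SD = 4.72 x √(89/2) / (1.96 + z).

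| Assumed power behind 89 | Implied SD | Power for 4.72 h at 178 per arm |
|---|---|---|
| 80% (z = 0.842) | 11.24 h | 97.7% |
| 90% (z = 1.282) | 9.71 h | 99.6% |

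With all 210 per arm analysed, the corresponding powers are 99.0% and 99.9%.

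**Reading 2: a separate comparison in each surgery type.** Each type has 105 per arm, 89 evaluable, which is what the calculation asks for.

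- With two independent tests at 5% and no true effect in either type, the chance of at least one false positive is 1 − 0.95² = 0.0975, or 9.75%. This counts one outcome only.
- If alpha were split to 2.5% per type with 89 evaluable per arm and the same implied SDs, power for 4.72 h would be 71% (SD 11.24 h) or 84% (SD 9.71 h).

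**Reading 3: one comparison of 105 per arm.** The total is 210 (178 evaluable), and 420 is simply wrong.

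**The case against.** The strongest reply is that this is an omitted step, not a wrong number. The sentence giving 420 names both operations and randomisation is stratified, so 2 x 2 x 105 is probably what was meant. The article is also condensed and refers to an additional file for the analysis, which may contain comparisons by surgery type. On the pooled reading the trial is larger than needed, not underpowered.

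Part of this stands. The intent is plausible, and nothing can be claimed about analyses in a file that is not shown. But the text derives 420 from a two-group calculation, and no unseen analysis repairs that derivation. The contradiction is between two sections of the same document.

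Several stronger readings are tempting and should be resisted:

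- **That rectal patients are shown to recover more slowly.** A reader might infer this from the 48–72 h given for the colon in the Background. That sentence compares organs after surgery, not operations, and it applies as much to the colon of a hysterectomy patient.
- **That the rectal stratum is underpowered.** The article gives no SD for that population, so no power figure for it can be derived.
- **That the planning data come from open surgery.** The article says transabdominal; anything further is inference.
- **That the missing SD and power are a fault in themselves.** An article may leave these to the full protocol, and the arithmetic point does not depend on them.
- **That the authors are free to choose the analysis after seeing results.** The only comparison described is the pooled one, which limits that freedom considerably.

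Whether two distinct surgical populations need joint alpha control can also be debated. The 9.75% is therefore a consequence to be addressed if per-type tests are chosen, not a proven defect of the present plan.

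**Conclusion.** The point holds. The stated total does not follow from the stated calculation: 2 x 105 is 210, and 420 requires a factor for surgery type that the article neither states nor carries into its analysis.

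Two results rest on the document's figures alone: the exact twofold gap, and the fall in detectable difference from 4.72 h to about 3.34 h if all 420 are pooled. The power figures of about 98% and 99.6% rest on assuming that 89 was sized for 80% or 90% power at two-sided 5%. They illustrate the gap and should not be written into the protocol as they stand. The 9.75% assumes one 5% test per surgery type on a single outcome, with no true effect in either.

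The planning data come from gynaecological surgery only, so any power stated for the rectal stratum would be an assumption. That limits what can be claimed, but it does not show that the stratum is too small.

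**What to change.** Rewrite Sample size estimation so that the total follows from the calculation, and align it with the statistical analysis section. One of three versions should be chosen:

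- **(a) Per-type design.** State that 420 = 2 arms x 2 surgery types x 105, name surgery type as the randomisation stratum, and prespecify the comparison within each type with its alpha handling. If alpha is split, restate the power per type.
- **(b) Pooled design.** Make one comparison, stratified by surgery type, the primary one. Restate the power or detectable difference for 210 per arm, using the SD actually used to obtain 89 and not one back-solved from an assumed power. Report by-type estimates as supportive.
- **(c) Smaller trial.** If one comparison of 105 per arm was meant, correct the total to 210.

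Under (a) or (b), add that the planning data are gynaecological, so that power in the rectal stratum is an assumption. Because recruitment is under way, the choice should be documented before the blind is broken. The cost is protocol wording and a restated size or power figure. No additional patients are needed.
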